## Sample size calculation

The initial analysis will be performed by intention to treat. We hypothesize that there is no difference in pain appreciation scores with the two sided test, an alpha of 0.05 and 90% power. In this equivalence design in each group 102 women have to be treated to exclude a potential clinical relevant difference of 10% (10 point scale, estimated SD 2.2). Allowing for 10% and 30 % cross-over/ non-compliance in the control group and experimental group respectively, 568 patients are required. When only 50 percent of all women need actually treatment 1136 women have to be randomized. We estimate that in the group of pregnant women who are willing to participate in the study 50% will actually need pain relief. This in contrast to the general Dutch pregnant population, which is known for a low uptake of pain relief during labor.

**4.4.1** Sample size for population of low risk pregnant women.

We hypothesize that there is no difference in pain appreciation scores with the two sided test, an alpha of 0.05 and 90% power. In this equivalence design in each group 102 women have to be treated to exclude a potential clinical relevant difference of 10% (10 point scale, estimated SD 2.2).

We estimate that in the group of pregnant women who are willing to participate in the study 50% actually need pain relief. Therefore 408 women have to be randomized.

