## Study procedures

Women will be asked to participate in this study before active labor has started, preferably during antenatal consult in the third trimester. They will be randomized and allocated to one of the treatment groups. If they request pain relief during labor they will be treated according to randomization with:

1. Remifentanil patient controlled analgesia; 30 microgram boluses, lockout time 3 minutes, maximum dose limit 1200 microgram/hour. Possibility of increasing or decreasing the bolus dose. When indicated EA is available.

2. Epidural analgesia; according to local protocol. When indicated RPCA is available.

There will be no additional invasive tests performed. Maternal vital parameters (temperature, heart rate, blood pressure, respiratory rate and pulse oxymetry) will be monitored non invasively at regular intervals. In the first hour after starting pain relief these parameters will be monitored with intervals of no longer than 15 minutes, after that with intervals of no longer than 1 hour. Maternal pulse oxymetry will also be monitored continuously.

Fetal heart rate and uterine activity will be measured continuously by external monitoring. When data are difficult to interpret or complications (such as meconium stained amniotic fluid, failure to progress in labor) occur, invasive monitoring by means of scalp electrode and intra-uterine pressure recording can be instituted.

Observations for known side effects will be made; respiratory depression, hypotension, nausea/vomiting and itching. Side effects will be managed by established local protocols.

Hypotension (systolic blood pressure < 90 mmHg or > 25% below baseline) will be treated with intravenous fluids, ephedrine 5 mg i.v. or phenylephrine 0.1 mg i.v. When oxygen saturation drops below 92% oxygen will be given.

Maternal pain score and pain appreciation score will be assessed using a visual analogue scale (VAS) ranging from 0-10. Women will be asked to mark the level of pain experienced during a contraction every hour starting at admission in the delivery room. Pain appreciation scores will be asked every hour, participating women will be asked to mark their level of satisfaction with analgesia. This will also be assessed using the visual analogue scale ranging from 0-10. After delivery an overall satisfaction score with pain(0-10) will be asked. Patient satisfaction will also be assessed by HADS and WDQ.

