  23. Apgar 1 and 5 minutes: continuous, quantitative
  24. Arterial umbilical cord pH: continuous, quantitative
  25. Admission to neonatal ward: categorical, quantitative (yes/no)
  26. Number of visits to/from primary health care mother: continuous, quantitative
  27. Number of visits to/from primary health care child: continuous, quantitative
  28. Number of visits to/from gynecologist: continuous, quantitative
  29. Number of visits to/from pediatrician: continuous, quantitative
  30. Duration of neonatal admission: continuous, quantitative

Duration of maternal admission: continuous, quantitative

We will report on the primary outcome measure, pain appreciation, as area under the pain appreciation curve (AUC), this as a measure for the aggregate effect of pain appreciation over a period of time (27). Total pain relief (TOTPAR) is a time weighted measure of AUC or total area under the pain appreciation curve and is a summary measure that integrates serial assessments of a subject’s pain appreciation over the duration of the study. The AUC will be analyzed from the start of active labor and for the whole duration of labor. We will also perform analysis from start of pain relief for the duration the pain relief is given. Subgroup analysis is planned for the AUC for 0-4 hours, 4-8 hours and >8 hours after the start of pain relief.

The trial is designed as an equivalence trial in which the null hypothesis

is that the difference in pain appreciation score between the two treatment groups is

greater than 10%. Preliminary data in perioperative patients on PCA opioid treatment show that changes (i.e. increases) in pain score of 10% or larger will prompt an action of the patient (i.e. she will require additional pain relief by pressing the PCA button). Extrapolating these data to the current study suggests that at VAS score differences of 10% or greater clinical differences in pain appreciation may be assumed.

The analysis of the randomised clinical trial will be by intention to treat, stratified for

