centre and parity. First, the epidural and remifentanil group will be compared. Relative risks and 95% confidence intervals will be calculated for the relevant outcome measures. Categorical variables will be tested with the Chi-square test or Fisher’s exact test. Continuous variables will be tested with the Mann-Whitney U test. Time to delivery will be assessed using Kaplan-Meier analysis. Pain scores will be analyzed separately. We will report on pain during labor (area under the curve and mean pain score), worst pain during labor, pain scores at request pain relief. The analysis will be repeated on a par protocol basis. Subsequently, planned subgroup analysis will be done for nulliparous versus parous women, previous caesarean section, preterm labor (32 to 34 weeks and 34-37 weeks) and term labor (37-42 weeks), spontaneous versus induced labor, maternal educational level, maternal age (under 35 years versus over 35 years), multiple pregnancy. We will then use decision analysis to evaluate which intervention strategy, ie epidural analgesia or remifentanil is preferred in women who need analgesia during labor.

The low risk women will be included and analyzed in a separate trial. In the Dutch system with midwifery care and home births, there might be a difference in expectation of women with regard to pain during labor.

To be able to convince both primary and secondary care providers, these groups will be analyzed separately.

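### The 1/(1 − 0.10 − 0.30)² cross-over inflation is superiority logic; in this equivalence design it raises the risk of a false equivalence claim, and the per-protocol analysis has no say in the conclusion

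*Protocol*

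**What the plan says.** Section 2 (Objectives) makes it the primary objective to test whether remifentanil PCA is as effective as epidural analgesia on pain appreciation. Section 8.1 says "The trial is designed as an equivalence trial in which the null hypothesis" is a between-group difference above 10%.

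Section 4.4 gives the design inputs: testing "with the two sided test, an alpha of 0.05 and 90% power", and "In this equivalence design in each group 102 women have to be treated" in order "to exclude a potential clinical relevant difference of 10% (10 point scale, estimated SD 2.2". It then states: "Allowing for 10% and 30 % cross-over/ non-compliance in the control group and experimental group respectively, 568 patients are required". It continues: "When only 50 percent of all women need actually treatment 1136 women have to be randomized".

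Sections 4.4 and 8.1 both make intention to treat the lead analysis. Section 8.1 adds "The analysis will be repeated on a par protocol basis" and says nothing about what follows if the two analyses disagree. Section 6.3 allows a change to the other method in either arm; for women allocated to RPCA it says "When indicated EA is available". Nowhere is the 10% margin reduced for the cross-over that the sample size anticipates.

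**The concern.** In a superiority trial, cross-over shrinks the difference one hopes to detect, and a larger trial makes up for it. In an equivalence trial the same shrinkage favours the claim. If the two analgesics truly differ, women who change method bring the arms closer together, and a larger sample only narrows the interval around a difference that is already too small.

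The protocol expects 10% and 30% non-compliance, inflates as if for superiority, keeps the margin, and leads with the analysis most exposed to the dilution. The per-protocol repeat, which could check it, has no role in the decision.

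The conclusion matters beyond the primary endpoint. Section 6.1.2 makes the cost comparison conditional on equivalence, and section 10.5 foresees that the results enter the guidelines of three professional societies.

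**Working it through.** **Inputs.** From section 4.4: margin 10% of a 10-point scale = 1.0 point; SD 2.2; alpha 0.05 two-sided; power 90%; 102 per group; non-compliance 10% (EA) and 30% (RPCA); 568 treated. Assumptions, because the protocol does not state them: 1:1 allocation; the outcome read as a mean score on the 10-point scale; equivalence declared when the 95% confidence interval lies within ±1.0 (nominal error 2.5% at the margin).

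**Reproducing the plan's figures.**
- Base: 2 × 2.2² × (1.960 + 1.282)² / 1.0² = 101.7, so 102 per group.
- Inflation: 102 / (1 − 0.10 − 0.30)² = 102 / 0.36 = 283.3, so 284 per group and 568 in total; 568 / 0.5 = 1136.
- Other corrections tried do not give 568: 102/0.9 + 102/0.7 = 259; 204/0.6 = 340; 204/(0.9 × 0.7) = 324; 204/(0.9 × 0.7)² = 514.

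**Is there power to restore?** With no true difference, cross-over leaves the expected intention-to-treat difference at zero. At 284 per group, SE = 2.2 × √(2/284) = 0.1846, and equivalence is declared when the observed difference is below 1 − 1.96 × 0.1846 = 0.638 in absolute value. Power = 2Φ(0.638/0.1846) − 1 = 99.95%, against the 90% planned.

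**False equivalence.** Let the true difference between the analgesics be 1.0, and let non-compliers lose a fraction *f* of the contrast over the whole AUC. The expected intention-to-treat difference is 1 − 0.40*f*. The chance of declaring equivalence is Φ((limit − difference)/SE); the opposite tail is negligible. At 102 per group, SE = 2.2 × √(2/102) = 0.308 and the limit is 1 − 1.96 × 0.308 = 0.396.

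| *f* | Diluted difference | 284 per group | 102 per group |
|---|---|---|---|
| 0 | 1.0 | 2.5% | 2.5% |
| 0.25 | 0.9 | 8% | 5% |
| 0.50 | 0.8 | 19% | 9% |
| 0.75 | 0.7 | 37% | 16% |
| 1 | 0.6 | 58% | 25% |

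A simulation of 40,000 trials at *f* = 1 gave 57%; the slight drop comes from the extra variance of mixed arms. With a 90% interval the *f* = 1 figure at 284 per group is 70%, against a nominal 5%.

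**When would 1/0.36 fit?** Only if the margin were cut to 0.6 as well. Then 284 per group gives 80% power at zero difference with a 95% interval, or 89% with a 90% interval.

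**Per-protocol set.** 0.9 × 284 = 256 EA and 0.7 × 284 = 199 RPCA. SE = 2.2 × √(1/255.6 + 1/198.8) = 0.208; power at zero difference = 2Φ(1/0.208 − 1.96) − 1 = 99.6%. In the same simulation, requiring both analyses brought the false-equivalence rate to 2.4%, with conversion unrelated to outcome.

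**If conversion depends on outcome.** Let women with lower scores be more likely to convert, with correlation 0.5 between score and a normal latent tendency. Removing 30% raises the RPCA mean by 0.5 × 2.2 × 0.497 = 0.55; removing 10% raises the EA mean by 0.5 × 2.2 × 0.195 = 0.21. A true difference of 1.0 in favour of EA becomes 1 − 0.55 + 0.21, about 0.67. The remaining SDs are about 2.06 and 2.12, so SE = √(2.06²/198.8 + 2.12²/255.6) = 0.197 and the limit is 1 − 1.96 × 0.197 = 0.614. The per-protocol analysis alone then declares equivalence with probability Φ((0.614 − 0.67)/0.197), about 39%.

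**The case against.** The strongest reply is that this is a strategy trial. The Summary words the aim as RPCA as first choice compared with EA, and section 6.3 makes the other method available in both arms. For that question, changing method is part of the policy, and intention to treat keeps its nominal error. This stands, and it limits the point to the primary objective in section 2, which is worded as a comparison of the two analgesics.

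Second, a reader might infer that women who fail on RPCA and convert are counted as RPCA successes. The protocol does not support that. It has no success classification; the outcome is an AUC of serial scores (sections 6.1.1 and 8.1), so a woman's poor scores before conversion stay in her result and count against RPCA. For the same reason, and because section 4.4 speaks of non-compliance as well as cross-over, 58% is an upper bound under these rates and not the expected error.

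Third, a per-protocol repeat is planned, and the definition of that set may properly be left to an SAP. Both are true. But the lead analysis, the inflation factor and the unreduced margin are fixed in the protocol itself.

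Fourth, some inflation is useful: keeping 102 women per protocol in the RPCA arm needs 102/0.7 = 146. That justifies allowing for exclusions, not the factor 1/0.36.

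Fifth, per-protocol agreement is no cure, because converters are not a random subset. This also stands, and the fix must not be presented as restoring the nominal rate.

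**Conclusion.** The point holds for the claim that remifentanil PCA is as effective as epidural analgesia. The step from 102 to 284 per group reproduces exactly as a superiority dilution correction. It answers a power loss that does not arise here at zero true difference, and it makes a false equivalence claim more likely at every level of dilution considered. When the analgesics truly differ by the margin, the risk with 284 per group runs from about 8% (diluted to 0.9) to at most 58% (diluted to 0.6), against a nominal 2.5%; with 102 per group it runs from 5% to 25%. The direction holds whenever cross-over dilutes a true difference. The size rests on the assumed 95% interval rule, an SD of 2.2, and how far non-compliers take on the other arm's scores.

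Two stronger conclusions do not follow. Intention to treat is not wrong for this trial, since it is the right analysis for the first-choice strategy. Nor is the trial too small for the rule proposed below. This should be fixed; it does not make the design unusable.

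**What to change.** - In section 8.1, state that equivalence of the two analgesics is concluded only if the confidence interval lies within ±1.0 in both the intention-to-treat analysis and the per-protocol analysis already planned. State the confidence level.
- State that intention to treat alone supports only the claim about RPCA as first-choice strategy.
- In section 4.4, replace the 1/0.36 justification with the power of the per-protocol set: 568 treated women leave about 256 EA and 199 RPCA, giving about 99.6% power at zero difference.

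The cost is wording in the protocol and SAP, with no extra patients. The rule is stricter, so equivalence is somewhat harder to claim. Because conversion may depend on how a woman is faring, the per-protocol result can itself be biased toward equivalence. The two-set rule can only lower the error, and the text should say that it does not guarantee the nominal rate.

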**SUMMARY**

**Rationale:** Epidural analgesia (EA) is considered to be the most effective method of pain relief during labor and is recommended as first method of pain relief by the Dutch Societies of Gynecologists and Anesthetists. In the Netherlands its uptake by pregnant women in labor of all ethnicities is still limited (10%), compared with other western countries (40-80%), mainly as a result of non-availability due to logistic problems.

**Objective**: To assess in women with a request for pain relief during labor the cost-effectiveness of remifentanil patient controlled analgesia (RPCA) as first choice compared to EA.

**Study design:** National multicenter randomized controlled trial (RCT), in 16 centers (university hospitals, teaching and non-teaching hospitals), in cooperation with midwifery practices.

**Study population:** Pregnant women, including low risk pregnant women under care of primary care midwives, will be offered to participate in the study. Only women who have been informed before active labor has started, will be eligible.

**Intervention:** Pregnant women with a request for pain relief during labor will be randomized before active labor has started to RPCA or EA.

**Main study parameters/endpoints:** The objective of this study is to test the hypothesis that remifentanil PCA is as effective as epidural analgesia with respect to pain appreciation scores. We will look at the following outcomes: costs, pain-appreciation, patient satisfaction, pain scores (pain-intensity), maternal and neonatal side effects.

**Analysis and sample size:** The initial analysis will be performed by intention to treat. We hypothesize that there is no difference in pain appreciation scores with the two sided test (alfa=0.05, power 1-beta=0.9). In this equivalence design in each group 102 women have to be treated to exclude a potential clinical relevant difference of 10% (10 point scale, estimated SD 2.2). After correction for cross-over and non-compliance 568 patients are required. When only 50 percent of all women need actually treatment 1136 women have to be randomized.

**Economical evaluation:** For both strategies the cost of perinatal care for mother and child of delivery and the next ten days after delivery will be registered and compared.

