This study will be a national multicenter RCT embedded within the Dutch Obstetric Consortium, in 16 centers (university hospitals, teaching and non-teaching hospitals) in cooperation with midwifery practices . Pregnant women will be randomized to RPCA or EA, before active labor has started and thereby will be informed on the assigned method of pain relief before labor starts (as in usual care). They will be only given pain relief during labor at their request or if a medical reason should arise.

Feasibility and compliance:

An ongoing study "Differences in maternal temperature and saturation after administration of remifentanil patient controlled analgesia (RCPA) or epidural analgesia (EA) during labor; STER study" in the Leiden University Medical Centre and in a recently published study on pain relief showed that randomization of women for the proposed methods of pain relief is feasible (22).

In the Netherlands, pain relief during labor is at present of major interest and an important topic for pregnant women, health care providers and politicians, as is pointed out in a recent publication of the multidisciplinary board on issues in obstetric management installed by the Dutch government. One of their advices is all Dutch women in labor should have access to

adequate pain relief during labor (23). Furthermore, the number of referrals to the hospital because of prolonged labor and request for pain relief in increasing, which will result in more women with a need of pain relief during labor. These developments will stimulate women to participate in studies on pain relief in labor.

We estimate that for proposed study for the inclusion of 1136 women in 27 months, at least 10 hospitals are needed. The collaborating hospitals have already 24 hours availability of epidural analgesia.

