## Randomisation, blinding and treatment allocation

Randomization stratified for centre and parity will take place after informed consent. Randomization will be performed through a web-based database located in the central data collection unit in the AMC in Amsterdam. Women will be randomly allocated to receive epidural analgesia of remifentanil PCA when they request pain relief during labor. There will be no blinding, as this is not possible with these two treatment methods.

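### Section 4.4.1 sizes the low-risk trial at 408 without the cross-over allowance used in section 4.4, and the protocol never says how the 408 relate to the 1136

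*Protocol*

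**What the plan says.** Sections 4.4 and 4.4.1 of the protocol start from the same design inputs: a two-sided test, "an alpha of 0.05 and 90% power", a margin of 10% on a 10-point scale, an SD of 2.2, 102 treated women per group, and half of the randomised women needing pain relief.

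Section 4.4 then allows for 10% (control) and 30% (experimental) cross-over or non-compliance. It arrives at 568 treated and 1136 randomised. Section 4.4.1, for low-risk women, goes straight from 102 per group to its total: "Therefore 408 women have to be randomized". It gives no cross-over rate and no reason for leaving the allowance out.

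On how the two numbers relate:

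- Section 8.1: "The low risk women will be included and analyzed in a separate trial". It adds that the groups are analysed separately so that both primary and secondary care providers can be convinced.
- Summary, study population: "Pregnant women, including low risk pregnant women under care of primary care midwives, will be offered to participate in the study". The only total in the Summary is 1136.
- Introduction, feasibility: "We estimate that for proposed study for the inclusion of 1136 women in 27 months, at least 10 hospitals are needed".
- Section 8.2 also refers only to 1136, as the number needed for sufficient power.

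Section 6.3 makes the other method available in both arms when indicated, with no exception for low-risk women.

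**The concern.** The two calculations share every input except the cross-over allowance, and that allowance nearly triples the main trial (204 to 568 treated). If cross-over has to be allowed for in one population, it needs either the same treatment or a stated reason for different treatment in the other, since the treatments and the rules for switching are the same. As written, section 4.4.1 attaches 90% power to a size that meets it, by the sponsor's own method, only if no low-risk woman crosses over.

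The low-risk result is meant to stand alone and to persuade primary care. If equivalence is not shown, or is shown in a heavily crossed-over sample, readers will judge the result against a stated power that section 4.4.1 does not support.

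The second part is bookkeeping with consequences. Without a statement that the 408 are inside or additional to the 1136, neither the total to be recruited nor the size of the main trial can be checked.

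**Working it through.** **Inputs.** From sections 4.4 and 4.4.1: two-sided alpha 0.05, power 90%, margin 1.0 point (10% of 10), SD 2.2, uptake 50%. From section 4.4 only: cross-over 10% and 30%. Allocation is 1:1, implied by equal groups.

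**1. Reproducing the protocol's figures.**

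- Per arm: 2 × (1.960 + 1.282)² × 2.2² / 1.0² = 101.7, so 102.
- Main trial: the treatment contrast shrinks by 1 − 0.10 − 0.30 = 0.6. Then 102 / 0.6² = 283.3, so 284 per arm, 568 treated, and 568 / 0.5 = 1136.
- A simple drop-out correction does not give 568 (102/0.9 + 102/0.7 = 259; 204/0.6 = 340), so the dilution factor is the method used.
- Low-risk: 2 × 102 / 0.5 = 408, with no dilution term.

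All four figures (102, 568, 1136, 408) reproduce exactly. With the 10%/30% allowance, section 4.4.1 would also give 568 treated and 1136 randomised.

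**2. Low-risk power by the protocol's dilution method.** SE = 2.2 × √(2/102) = 0.308. Power = Φ(k/0.308 − 1.96), where k = 1 − c₁ − c₂ is the diluted 1.0-point difference. Only the first and last rows use rates that section 4.4.1 implies or section 4.4 states. The others are assumed, to show the range.

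| Cross-over (control/experimental) | k | Power, 102 treated per arm | Randomised for 90% |
|---|---|---|---|
| none | 1.00 | 90% | 408 |
| 5%/10% | 0.85 | 79% | 568 |
| 5%/15% | 0.80 | 74% | 640 |
| 10%/20% | 0.70 | 62% | 836 |
| 10%/30% | 0.60 | 50% | 1136 |

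**3. Per-protocol repeat.** Losing 10% and 30% of 102 leaves about 92 and 71 women. SE = 2.2 × √(1/92 + 1/71) = 0.348.

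- By the formula that reproduces 102: Φ(1/0.348 − 1.96) = 82%.
- If both equivalence bounds must be met, at a true difference of zero: 64% with a 95% CI, 78% with a 90% CI.

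**4. Intention-to-treat equivalence.** With a fixed margin of 1.0 and a true difference of zero, the expected difference stays zero under cross-over, so power is not lowered. Dilution acts on the error side. If the true difference is 1.0, diluted to 0.6, then with 102 per arm equivalence would be declared about 25% of the time with a 95% CI, and 36% with a 90% CI. A larger sample does not remove this: with 284 per arm the same chances are 58% and 70%.

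**5. Relation of 408 to 1136.**

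- Additional: 1136 + 408 = 1544, and 1544/1136 = 1.36. The main trial keeps its 90%.
- Inside: 1136 − 408 = 728 randomised, 728/4 = 182 treated per arm. SE = 2.2 × √(2/182) = 0.231, and Φ(0.6/0.231 − 1.96) = 74%.

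**The case against.** The strongest reply is that the initial analysis is intention to treat in an equivalence design. If the treatments truly do not differ, cross-over does not reduce the chance of showing equivalence, so the missing allowance need not cost power. This stands. The 50% to 79% figures are the protocol's own detection-of-difference calculation applied consistently; they are not the power of the intention-to-treat equivalence test at a zero difference. The reply does not rescue section 4.4.1, because section 4.4 uses the dilution method for the main trial, and because dilution in the intention-to-treat analysis makes false equivalence easier.

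A second reply is that the 10% and 30% rates are given for the main trial only. That also stands, which is why a range is shown. But section 4.4.1 neither states a lower rate nor says that one is expected.

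Third, a reader might infer that either the total or the main trial's size must be wrong. The documents do not support that. A separately numbered sample size and the words in section 8.1 make 1136 plus 408 the more natural reading, and on it 1136 stands for the main trial. The Summary says that low-risk women will be approached; it does not say that the 1136 counts them.

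Finally, separate analysis might seem to call for stratifying randomisation by risk group. Section 6.2 stratifies by centre and parity. Analysing separately a group defined before randomisation is valid without stratifying on it, so this would be a preference and is not part of the point.

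**Conclusion.** The point holds in two parts.

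First, section 4.4.1 omits, without a reason, an allowance that section 4.4 treats as necessary on otherwise identical inputs. By the protocol's own method, 408 randomised supports 90% power only with no cross-over. It supports about 50% at the main trial's rates and 62% to 79% at the milder assumed rates. The per-protocol repeat has about 82% at 10%/30% by the formula behind 102, and 64% to 78% if both bounds are required, depending on the confidence level.

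A reader might go further and put one replacement figure on the low-risk power, such as 64%, or a ceiling of 80%. The documents do not fix what that requires. The 64% presumes a 95% CI, both bounds and the per-protocol set. The 80% is the two-bound power of 102 per arm with a 95% CI and no cross-over at all, so it is no measure of this omission.

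Second, the relation between 408 and 1136 is unstated. If the 408 are additional, the main trial is unaffected but the recruitment plan leaves out 408 women. If they are inside, the main trial falls to about 74% by the same method. The wording favours the first reading without settling it.

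**What to change.** - In section 4.4.1, state the cross-over rates expected in low-risk women and restate the power at 408 under them, or give the reason for omitting the allowance.
- Unless the size is changed, present the low-risk result as an estimate with its 95% CI, and mention that cross-over dilutes a true difference in the intention-to-treat comparison.
- State whether the 408 are additional to the 1136 or part of it, and give one total. Align the Summary, the feasibility paragraph of the Introduction and section 8.2 with it.

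The cost is mainly text. If the 408 are additional, the recruitment plan (hospitals and the 27 months) has to cover 1544 women. If they are inside, the main trial's power has to be restated for 728. Enlarging the low-risk trial is an option for the sponsor, but it is costly: the full 10%/30% allowance means 1136 low-risk women, or 1136 + 1136 = 2272 in all if they are additional.
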